**Materials/methods:**

This is an open-label, single-arm phase 2 trial. Eligible patients have metastatic melanoma with ≤10 extracranial oligoprogressive sites while on first-line systemic therapy. Oligoprogression is defined using modified RECIST 1.1 or PERCIST criteria. All oligoprogressive sites will receive SBRT per institutional guidelines, typically delivered over 3 fractions. Patients will stay on current systemic therapy. The primary endpoint is PFS defined as the time from enrollment to the date of further disease progression. Secondary endpoints include overall survival, time on current systemic therapy, out-of-field response, tolerance of SBRT, and quality of life (QOL). In addition, serial blood samples are collected for exploratory analyses of circulating tumor DNA (ctDNA), mutant allele fraction, and immune profiling (including CD8+ T-cell subsets). The trial aims to enroll 52 patients over 12 months with additional 24 months of follow-up.

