### Assessments and follow-up

The schedule of study assessments is summarized in **Table 2**. Baseline evaluations: At study entry, baseline tumor assessments are documented using imaging (CT, PET/CT and/or MRI) performed within 6 weeks prior to enrollment​. This imaging serves as the reference for measuring treatment response and progression going forward. Patients also complete baseline patient-reported outcome questionnaires (PRO-CTCAE, EORTC-QLQ-C30). Baseline blood samples are drawn and banked for exploratory biomarker studies.

**Table 2 T2:** Study timeline.

Required investigation	Pre-study (prior to enrolment)	Before 1st fraction of radiation	First follow-up after radiation (4 weeks ± 2 weeks)	Subsequent follow-up (every 12 ± 2 weeks until 104 weeks)
History and physical exam				
ECOG		X	X	X
Weight		X	X	X
Radiology				
CT CAP or PET/CT	Within ≤42 d			X
CT or MRI Brain (optional)	Within ≤42 d			If indicated
Specimen collection				
Blood collection		X	X	At the time of progression
Adverse events				
Survival status			X	X
CTCAE v5.0		X	X	X
Quality of life				
PRO-CTCAE		X	X	X
EORTC-QLQ-C30		X	X	X

Treatment and follow-up visits: During radiation delivery (which spans up to two weeks), patients are seen regularly for treatment management. An acute toxicity evaluation is performed at the end of the radiation treatment course (within a week of completing radiotherapy). Thereafter, follow-up visits are scheduled at approximately 8 weeks post-radiation, and then every 3 months for the first year, or until further disease progression. At each follow-up, a clinical examination and toxicity assessment are conducted. Adverse events are graded according to NCI CTCAE v5.0. In addition, patients complete PRO-CTCAE questionnaires to capture symptoms and side effects from the patient’s perspective, and the EORTC quality-of-life questionnaires are repeated at defined intervals (e.g. 3, 6, 12 months) to assess any changes in global health status and specific symptoms over time.

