### Statistical analysis

As reviewed in the literature, first-line therapy with immune checkpoint inhibitors results in a mPFS of 11.5 months (12). Our study was designed with the expectation that we would observe a median PFS improvement of about 7 months with addition of SBRT. Assuming an enrolment time of 12 months and follow-up of 24 months, 15% drop out and another 15% of screen failure, a sample size of 52 patients will achieve 85% power at 0.05 significance level to detect a median PFS of 7 months based on a two-sided, single arm log-rank test.

PFS/OS will be estimated using Kaplan-Meier (KM) method and presented graphically. The cumulative incidences of change in systemic therapy and acute/late toxicity will be estimated using the Aalen-Johansen method, where mortality without events of interest will be treated as competing event. Univariate Cox proportional hazard models will also be conducted to examine the association of PFS/OS with patient and tumor characteristics of interest, such as age, sex and the number of oligoprogressive lesions treated, BRAF mutational status, and type of first-line systemic therapy. Similarly, the univariate Fine-Gray competing risk models will be applied to examine the association of time to change in systemic therapy/acute/late toxicity with the patient and tumor characteristics of interests. Multivariable analyses (MVA) will also be conducted to determine the association if applicable. The change in QOL scores at follow ups from baseline (before SBRT) will be analyzed using linear mixed-effect models and the change in scores of >10 points would be deemed a minimal clinically important difference. The other categorical secondary outcomes (e.g. Out of field response, AE) will be summarized using frequency counts and proportion.

An interim analysis will be conducted after the first 25 patients have been enrolled and followed for at least 6 months, to assess safety and early efficacy trends. If ≥30% of patients experience grade 3 or higher toxicities deemed related to SBRT at that time, early termination of the trial will be considered.

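### The 85% power most naturally rests on 24 to 36 months of observation per patient, but Table 2 schedules assessments only to 104 weeks; if PFS observation ends there, power falls by about 3 to 5 points

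*Protocol article*

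**What the plan says.** The sample-size paragraph (Protocol article, Statistical analysis) takes its time inputs as "Assuming an enrolment time of 12 months and follow-up of 24 months" and concludes that "a sample size of 52 patients will achieve 85% power at 0.05 significance level", "based on a two-sided, single arm log-rank test". The same sentence assumes 15% drop-out and a further 15% screen failure. The abstract (Materials/methods) gives the timeline as "The trial aims to enroll 52 patients over 12 months with additional 24 months of follow-up".

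Table 2 (Assessments and follow-up) is the schedule of required investigations. Its last column, which holds repeat CT or PET/CT and survival status, is headed "Subsequent follow-up (every 12 ± 2 weeks until 104 weeks". The running text beside the table describes three-monthly visits for the first year only. The paragraph on radiologic assessments gives imaging about every 12 weeks, in line with standard melanoma follow-up, with no end date.

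**The concern.** The power of a one-sample log-rank test depends on the number of events, and so on how long each patient is observed. An accrual period matters in such a calculation only if patients are observed for different lengths of time. Twelve months of accrual followed by 24 more months means that the first patient is observed for 36 months and the last for 24. Under Table 2 each patient's scheduled assessments end at 104 weeks (104 × 7 / 30.44 = 23.9 months). Events that early enrollees would have between about month 24 and month 36 would then count towards the planned power although no scheduled assessment would find them. At stake is whether the primary endpoint has the power stated for it.

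**Working it through.** **Inputs.**
- Benchmark median 11.5 months: "first-line therapy with immune checkpoint inhibitors results in a mPFS of 11.5 months".
- Alternative 18.5 months = 11.5 + 7: "we would observe a median PFS improvement of about 7 months with addition of SBRT". The same paragraph also says "to detect a median PFS of 7 months based on a two-sided, single arm log-rank test". I read that 7 as the improvement, because a literal alternative of 7 months would need a benchmark that the document does not give.
- n = 52, two-sided 0.05, from the power sentence.
- Assumptions of mine: exponential PFS, uniform entry over 12 months, all 52 evaluable, no losses.

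**Rates.** λ0 = ln 2 / 11.5 = 0.0603 per month; λ1 = ln 2 / 18.5 = 0.0375 per month; hazard ratio 11.5 / 18.5 = 0.622.

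**Expected events under the alternative.**
- Cut-off at month 36: 52 × [1 − (e^(−24λ1) − e^(−36λ1)) / (12λ1)] = 35.0.
- Stop at 104 weeks: 52 × [1 − e^(−23.9λ1)] = 30.8.

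**Test.** Z = (E − O) / √V, rejecting in favour of longer PFS when Z > 1.96. O is the observed number of events and E the number expected at the benchmark hazard. Under the alternative the mean of E is the mean of O divided by 0.622. With V = (O+E)/2:
- Month 36: E = 56.2, E − O = 21.3, V = 45.6, so 21.3 / √45.6 = 3.15.
- 104 weeks: E = 49.5, E − O = 18.7, V = 40.1, so 18.7 / √40.1 = 2.96.

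Under the alternative, E − O varies more than √V allows, so Φ(3.15 − 1.96) = 88% is too high. Power was therefore simulated (60,000 to 100,000 trials per setting):

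| Observation per patient | Events | V=(O+E)/2 | V=E | V=O |
|---|---|---|---|---|
| 24 to 36 months | 35.0 | 85.8% | 82.5% | 88.5% |
| 104 weeks from entry | 30.8 | 82% | 78% | 85.4% |
| 25 to 26 months from entry | – | 83–84% | 79–80% | – |

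The last row covers the case in which the 104 weeks run from radiation.

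**Reproducing the 85%.** Month 36, all 52 evaluable and V=(O+E)/2 give 85.8%. V=E starts at about 82.5%, so its 78% is not a fall from 85%.

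**Size of the loss.** 85.8 − 82 ≈ 4 points; 82.5 − 78 ≈ 4.5; 88.5 − 85.4 ≈ 3. A log-hazard formula gives 80.3% and 75.2%, a loss of 5. If the 104 weeks run from radiation the loss is about 2 to 4 points.

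**Attrition.** If the 52 includes the stated losses, the evaluable number is 52 × 0.85 = 44 after one of them and 44.2 × 0.85 ≈ 37 after both. With 44, power with V=E and V=(O+E)/2 is about 76% and 80% to month 36, and about 70% and 76% to 104 weeks. With 37 it is about 68% and 73%, and about 63% and 69%.

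**The case against.** The strongest reply is that 24 months can mean 24 months for each patient. That equals 104 weeks, so the power statement and Table 2 would agree. The abstract does not exclude this: if the last patient enters at month 12 and is followed for 24 months, the trial also lasts 12 plus 24 months. This stands as far as it goes, and the 24-to-36-month reading is an inference, though the more natural one. It does not rescue the 85%, however. At 24 months per patient, V=(O+E)/2 gives 82% and V=E gives 78%. V=O reaches 85.4%, but its upper-tail error is about 3.5% to 3.7% against a nominal 2.5%. A Wald test on the median gives 84.8%, but that is not the log-rank test the plan names.

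Two stronger readings are tempting, and the document does not support them.
- A reader might infer that Table 2 stops every patient at 104 weeks, so that later events are lost. Table 2 limits scheduled assessments. It states no censoring rule or data cut-off, the imaging paragraph sets no end date, and scans done in standard care could still supply those events.
- A reader might infer that the trial's power is 82%, or 78%, instead of 85%. The test variance is not stated, the 78% belongs to a form that never reached 85%, and both figures leave out the drop-out and screen failure named in the same sentence. Attrition could matter more than the follow-up length.

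It is also fair to say that a few points of power will not change how a single-arm phase 2 trial, described by its authors as hypothesis-generating, is interpreted.

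**Conclusion.** The concern holds in conditional form. The stated 85% is matched by observation to about month 36 with all 52 patients evaluable and V=(O+E)/2, and the schedule in Table 2 does not provide that observation. If PFS observation ends at 104 weeks, expected events fall from 35.0 to about 31 and power falls by about 3 to 5 points, to about 82% at best with V=(O+E)/2. If 24 months per patient was intended, there is no conflict over follow-up length, but the log-rank forms that do not inflate the type I error still give less than 85%. Either reading calls for a correction. The result rests on exponential PFS, medians of 11.5 and 18.5 months, and no losses; any losses taken out of the 52 lower the power further. The effect is modest, but it concerns the primary endpoint and is cheap to put right.

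**What to change.** Choose one of two changes.

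1. Follow progression and survival status to a common cut-off 24 months after the last enrolment, and change the end point in the last column of Table 2 to match. The cost is up to about four further 12-weekly scans (52 / 12 ≈ 4.3) for the earliest patients still progression-free, on a schedule the article already aligns with standard follow-up. No more patients are needed for this change.
2. Keep 104 weeks, say whether it runs from enrolment or from radiation, and restate the power computed for that follow-up. Give the variance form and the evaluable number after drop-out and screen failure. This costs a sentence or two. The 82% should not simply be substituted for 85%, because it assumes 52 evaluable patients. Holding 85% with the 104-week stop and V=(O+E)/2 would take about 57 to 58 evaluable patients.

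In either case, reconcile the first-year visit wording in Assessments and follow-up with the follow-up length chosen. If follow-up really stopped at 12 months, the log-hazard formula, which gives 80.3% to month 36, would give only about 54% with 52 patients.

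### For a gain from 11.5 to 18.5 months, 52 patients leave no margin for the stated losses: power is about 74–83% if 52 are enrolled, about 67–77% if 52 are screened, not 85%

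*Protocol article*

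**What the plan says.** All of the design figures are in the Statistical analysis section of the protocol article.

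- Historical reference: "first-line therapy with immune checkpoint inhibitors results in a mPFS of 11.5 months".
- Expected effect: "we would observe a median PFS improvement of about 7 months with addition of SBRT".
- Timing: "Assuming an enrolment time of 12 months and follow-up of 24 months".
- Losses, size and power in one clause: "15% drop out and another 15% of screen failure, a sample size of 52 patients will achieve 85% power".
- Test: "based on a two-sided, single arm log-rank test", at the 0.05 level.
- Target, stated a second time in the same sentence: "to detect a median PFS of 7 months".

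The abstract (Materials/methods) adds what the 52 appears to count: "The trial aims to enroll 52 patients over 12 months with additional 24 months of follow-up". The article prints no alternative median, no evaluable number and no expected number of events. It does not say how drop-out or screen failure enters the calculation.

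**The concern.** The wording makes 15% drop-out and a further 15% screen failure assumptions of the 85%. A reader will take it that 52 has been inflated for both and that power after losses is still 85%. If 52 is instead about the number needed with no losses, the trial runs a larger risk of missing its target effect than the 15% implied. This is the only justification given for the size of the primary PFS comparison, so it also governs how much weight a non-significant result can bear.

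Two further features make the figure hard to verify. The target effect is worded in two incompatible ways, and screen failure is listed as an input to power although the abstract says 52 patients will be enrolled.

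**Working it through.** **Inputs.** From the Statistical analysis section: null median m0 = 11.5 months, gain of about 7 months, 12 months' enrolment, 24 months' further follow-up, two-sided 0.05. Inferred: alternative median m1 = 11.5 + 7 = 18.5 months, hazard ratio 11.5/18.5 = 0.62. Assumed: exponential PFS and uniform accrual.

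**Per-patient quantities under the alternative.** Hazards are λ0 = ln2/11.5 and λ1 = ln2/18.5 = 0.03747.

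- Probability of an observed event: p1 = 1 − e^(−24λ1)(1 − e^(−12λ1))/(12λ1) = 1 − 0.4069 × 0.8054 = 0.672.
- Expected events under the null: p0 = p1 × λ0/λ1 = 0.672 × 18.5/11.5 = 1.082.
- Variance of O − E for one patient: v = p1 + λ0²E[X²] − 2λ0E[δX] − (p1 − p0)² = 1.111, where X is follow-up time and δ the event indicator.

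**Power** = Φ{[√n(p0 − p1) − 1.96√s]/√v}. The modified test takes s = (p0 + p1)/2 = 0.877, that is, variance (O+E)/2. The classic test takes s = p0 = 1.082, that is, variance E.

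**Reproducing the stated figure: n = 52, no losses.** √52 × 0.409 = 2.951.

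- Modified: (2.951 − 1.835)/1.054 = 1.06, power 85.5%.
- Classic: (2.951 − 2.038)/1.054 = 0.87, power 80.7%.

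Solving for 85% gives n = 51.2 (modified) or 58.5 (classic). Simulation with 100,000 runs at n = 52 gives 85.7% and 82.5%. Expected events are 52 × 0.672, about 35. The printed 85% therefore matches 52 fully followed patients with the modified variance. With the classic variance, 52 falls short even before any loss.

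**Applying the stated losses.** Removing drop-outs leaves 52 × 0.85 = 44.2. Removing both losses leaves 52 × 0.85 × 0.85 = 37.6 (36.4 if the two percentages are added). For censoring, drop-out is taken as exponential with 15% lost by 24 months, which is an assumption because the article gives no time scale.

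| What 52 counts | How drop-out enters | Patients | Power, modified | Power, classic |
|---|---|---|---|---|
| No losses | – | 52 | 85.5% | 80.7% |
| Enrolled | censored | 52 | 82.9% | 77.6% |
| Enrolled | removed | 44.2 | 80.0% | 74.1% |
| Screened | censored | 44.2 | 77.1% | 70.8% |
| Screened | removed | 37.6 | 73.8% | 67.2% |

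Simulation agrees within about 2 points: 83.1%/79.3% for 52 with censoring, 80.0%/75.6% for 44, 77.1%/72.2% for 44 with censoring, and 74.5%/69.2% for 38.

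**Detectable median.** Solving the same formula for the m1 that gives 85% with 37.6 patients yields about 20.1 months (modified) to 21.2 months (classic), against 18.5.

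**The second wording of the effect.** If the target is a median of 7 months tested against 11.5, 37.6 patients give about 80% (modified) or 88% (classic) by formula; simulation with 38 gives about 80–85%.

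**The case against.** A reader might infer that power is simply about 74% or lower. That is the worst case. It needs both losses to come out of the 52 and drop-outs to contribute no follow-up. The abstract says 52 will be enrolled, PFS is counted from enrolment, and screen failures normally precede enrolment. Nothing in the article excludes drop-outs from a time-to-event analysis, where they would ordinarily be censored. On that reading, with the variance that reproduces 85%, the shortfall is only about 2 to 3 points. This objection stands, and it is why the result is given as a range led by the enrolled-52 case.

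A reader might also infer that the allowance for losses was forgotten. The article does not show that. The match at 51.2 depends on one variance form, and neither the form nor the software is named. What can be said is that, for the described improvement, 52 contains no visible allowance.

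The alternative of 18.5 months is inferred. Taken literally, a target of 7 months against 11.5 would let about 38 evaluable patients come close to 85%, so 52 could then already include both losses. But that test would detect a shorter PFS, contrary to the trial's hypothesis of a meaningful extension. It does not rescue the figure; it shows that the target must be corrected.

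Finally, the Discussion calls the outcomes hypothesis-generating, which lowers the stakes. Nor is it a fault that an article omits computational detail. The point here is different: the article prints inputs and a result, and the result does not follow from the inputs.

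**Conclusion.** The point holds in a limited form. For 11.5 to 18.5 months at two-sided 0.05, every way examined of applying the stated drop-out gives less than 85%. If 52 is the enrolled count, power is about 78–83% with drop-outs censored or 74–80% with drop-outs removed, so the chance of missing the target effect is about 17–26% rather than 15%. If 52 counts screened patients, power is about 71–77% or 67–74% respectively, a miss risk of about 23–33%.

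The ranges span the two variance forms. They rest on exponential PFS, uniform accrual, the inferred alternative of 18.5 months and, for censoring, 15% lost by 24 months. The documents do not support a single replacement figure, because they settle neither the variance, nor how losses enter, nor, in words, the target effect.

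**What to change.** Keep 52 patients and rewrite the sample-size sentence so that it can be reproduced:

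1. State the null and alternative medians, and correct the clause that gives the target as a median of 7 months.
2. Name the variance form of the one-sample log-rank test.
3. Say whether 52 is screened or enrolled. If enrolled, take screen failure out of the power assumptions and report it as a recruitment figure.
4. Say whether drop-outs are censored or removed, over what period the 15% applies, and how many events are expected (about 35 with no losses, about 32 with drop-outs censored at 52 enrolled: 52 × 0.620).
5. Restate the power to match: about 74–83% if 52 are enrolled, about 67–77% if 52 are screened. Alternatively, restate the median detectable at 85%.

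This changes wording only. No extra patients are asked for; for orientation, holding 85% after removing both losses would take about 71 screened patients (modified variance) to 82 (classic). The cost is a less favourable stated power.

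### The sample-size statement contradicts itself: it expects a 7-month gain over 11.5 months, then powers the trial for a median PFS of 7 months, and 52 patients does not show which was meant

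*Protocol article*

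**What the plan says.** Three consecutive sentences in the protocol article, Statistical analysis, set the design.

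- The benchmark: "first-line therapy with immune checkpoint inhibitors results in a mPFS of 11.5 months". It is the only reference median in that paragraph, but it is not called the null value of the test.
- The effect: "Our study was designed with the expectation that we would observe a median PFS improvement of about 7 months with addition of SBRT".
- The power claim, for a sample of 52, is that it "will achieve 85% power at 0.05 significance level to detect a median PFS of 7 months based on a two-sided, single arm log-rank test". The same sentence gives the timing ("Assuming an enrolment time of 12 months and follow-up of 24 months") and allows 15% for drop-out and a further 15% for screen failure.

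The section on study design, outcomes and end-points states the primary hypothesis in words: adding radiotherapy is expected to lengthen PFS. The Abstract describes 52 as the number to be enrolled and makes the 24 months additional to the 12 months of accrual.

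**The concern.** The effect sentence uses 7 months as a difference and the power sentence uses it as a median. Both cannot describe the same alternative. Added to 11.5, a 7-month gain gives 18.5 months, a hazard ratio of 11.5/18.5 = 0.62 under exponential PFS. A median of 7 months gives 11.5/7 = 1.64, which is a worsening. Because the test is two-sided, a true median of 7 months against 11.5 would tend to produce a significant result in the wrong direction.

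In a single-arm trial the null and target medians carry the whole meaning of the primary result. The Discussion says a positive efficacy signal would justify a randomised trial. If the reference is not fixed in advance, it can be chosen once the observed median is known. The sample size is also affected, since it cannot be verified without knowing which two medians went into it.

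**Working it through.** **Inputs from the Statistical analysis section:** medians 11.5 and 7 months, an improvement of 7 months (so 18.5), power 85%, two-sided alpha 0.05, one-sample log-rank test, accrual 12 months plus 24 months of follow-up, 15% drop-out, 15% screen failure, N = 52.

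**Assumptions (not in the document):** exponential PFS and uniform accrual.

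**Quantities.** z_a = 1.960 and z_b = 1.036. Hazard λ = ln 2 / median, with 0 for the null and 1 for the alternative; r = λ1/λ0.

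Probability of an event under the alternative: p = 1 − [exp(−24λ1) − exp(−36λ1)] / (12λ1). Expected null events per patient: e = p/r. Let v be the variance, under the alternative, of a patient's observed minus expected events (obtained by simulation).

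| Null → alternative | r | p | e | v |
|---|---|---|---|---|
| 11.5 → 18.5 | 0.622 | 0.672 | 1.082 | 1.112 |
| 11.5 → 7 | 1.643 | 0.946 | 0.576 | 0.431 |
| 7 → 11.5 | 0.609 | 0.833 | 1.368 | 1.681 |

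**Four usual forms of the evaluable sample size:**

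- (a) log hazard ratio: n = (z_a + z_b)² / [(ln r)² p]
- (b) null variance: n = (z_a + z_b√r)² / [(1 − r)² e]
- (c) exact variance: n = (z_a√e + z_b√v)² / (p − e)²
- (d) as (c), with (p + e)/2 in place of e in the z_a term

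Example, (a) for 11.5 → 18.5: (2.996)² / (0.4754)² = 39.7 events; 39.7 / 0.672 = 59.1, so 60 patients.

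**Reproducing 52.** Each cell gives evaluable patients, then the number after dividing by 0.85² = 0.7225 for the two allowances, rounded up.

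| Null → alternative | (a) | (b) | (c) | (d) |
|---|---|---|---|---|
| 11.5 → 7 | 39; 54 | 46; 64 | 35; 49 | 42; 59 |
| 7 → 11.5 | 44; 61 | 37; 52 | 47; 66 | 41; 57 |
| 11.5 → 18.5 | 60; 84 | 50; 70 | 59; 82 | 52; 72 |

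- Read literally, 11.5 against 7 brackets 52 once attrition is included (49 to 64).
- With 7 as the null and 11.5 as the target, form (b) gives exactly 52 with attrition; the other forms give 57 to 66.
- For 11.5 against 18.5, 50 or 52 appears only before attrition. With it, N is 70 to 84, or up to 86 if the allowances are applied as one division by 0.70 (60/0.70 = 85.7).

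**Power at the stated size.** From 52, one 15% loss leaves 52 × 0.85 = 44; two leave 52 × 0.7225 = 38. I simulated 40,000 trials per case, dividing observed minus expected events by √E or by √[(O + E)/2]. The range covers both versions.

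| Evaluable | True 18.5, null 11.5: rejects toward longer PFS | True 7, null 11.5: rejects toward shorter PFS |
|---|---|---|
| 52 | 82-86% | 91-94% |
| 44 | 76-80% | 86-90% |
| 38 | 69-74% | about 80-85% |

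With a true median of 7 months against 11.5, rejection toward longer PFS was essentially 0% at every size.

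**The case against.** The best defence is a dropped word. If the power sentence was meant to repeat the improvement of about 7 months from the sentence before it, the conflict of direction disappears. The Introduction, the hypothesis and the Discussion all speak of extending PFS, so no careful reader would call a significantly shorter PFS a success. This is plausible, but it does not rescue the stated figure: 18.5 against 11.5 reaches 85% at 52 only if nobody is lost, and the same sentence allows for losses.

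Nor can 11.5 be taken for granted as the null. The article never labels it so, and the Introduction cites a median of 7 months for TIL therapy after progression on immunotherapy. Seven months could therefore have been a benchmark, although a step from 7 to 11.5 is a gain of 4.5 months, not about 7. An unstated null of roughly 4.1 to 4.6 months would make 7 months a favourable target with 85% power, but no such figure appears in the article. These alternatives stand as possibilities, and they are why N cannot identify the hypothesis.

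It is also fair that the 44 and 38 scenarios are somewhat pessimistic, because patients who drop out contribute some follow-up. And if screen failures fall outside the 52, as the Abstract's reference to enrolment might suggest, 38 is too low.

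**Conclusion.** The contradiction is certain from the text alone: the alternative in the power sentence is 4.5 months below the only benchmark in the paragraph and opposite in direction to the hypothesis. The power figures rest on exponential PFS, uniform accrual and treating lost patients as uninformative. If 11.5 against 18.5 was intended, the claimed 85% becomes about 82-86%, 76-80% or 69-74%, depending on whether 52, 44 or 38 patients are evaluable.

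Three stronger readings are tempting, and the document does not support them.

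- A reader might infer that the primary hypothesis or the success criterion is wrong. The verbal hypothesis is correctly directed. The article states no numerical success criterion, which a condensed article may leave to the full protocol or analysis plan.
- A reader might infer that the trial was in fact sized to detect harm. The literal reading fits 52, but so does another, so this cannot be shown.
- A reader might infer that 18.5 months is plainly what was meant because 85% reproduces. It does so only in some forms and with both attrition allowances dropped.

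**What to change.** Replace the power sentence with one that states:

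- the null median PFS and its source;
- the target median PFS;
- that only rejection toward longer PFS counts as positive;
- whether 52 is before or after the 15% drop-out and the 15% screen failure;
- the power recalculated on that basis, with the survival distribution assumed.

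If 11.5 against 18.5 months was intended, do not simply insert 18.5 beside 52 and 85%, which would leave an incorrect power claim. Either restate the power as in the verdict or, if 85% is to be kept after both allowances, enlarge N to about 70 to 86. If another null was used, give it.

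Restating costs a few sentences and possibly a less favourable stated power. Only enlarging N would have an operational cost. The wording should be settled before any PFS data are examined.

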Treatments are delivered using image-guided radiotherapy on dedicated linear accelerators. SBRT to multiple lesions may be given sequentially or concurrently, at the discretion of the treating radiation oncologist, but the aim is to complete radiation to all sites as soon as feasible, preferably within two weeks of enrollment. Radiation therapy is typically given during the “off week” of systemic therapy to avoid treatment interruption; this timing is logistical rather than biological, and no drug holiday is planned. Thus, patients continue on their systemic treatment beyond progression, with the intent that eliminating the resistant lesions will allow the systemic treatment to remain effective for the other sites. All radiotherapy and medical oncology interventions in this study are standard modalities - SBRT is an established technique, and the drug regimens are the current standard of care for first-line treatment. Supportive care is provided as needed, and any toxicity from radiation or systemic therapy is managed per usual clinical practice.

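### On the planned accrual, the one formal safety look comes when about 51 of 52 patients are enrolled, so its stopping rule can spare very few

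*Protocol article*

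**What the plan says.** The Statistical analysis section sets a single interim analysis, meant to assess safety and early efficacy trends: "An interim analysis will be conducted after the first 25 patients have been enrolled and followed for at least 6 months". The rule attached to it is: "If ≥30% of patients experience grade 3 or higher toxicities deemed related to SBRT at that time, early termination of the trial will be considered".

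The abstract gives the accrual plan: "The trial aims to enroll 52 patients over 12 months with additional 24 months of follow-up". The sample-size paragraph repeats the 12-month enrolment time: "Assuming an enrolment time of 12 months and follow-up of 24 months, 15% drop out and another 15% of screen failure". On the timing of radiation, the Treatment intervention section says that "the aim is to complete radiation to all sites as soon as feasible, preferably within two weeks of enrollment".

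Other safety provisions are described. The section on design and end-points says that the centre's clinical trials unit monitors the study, including for safety. Assessments and follow-up provides for regular visits during radiation, an acute toxicity evaluation within a week of its end, and a toxicity assessment at every follow-up visit. None of these carries a numerical threshold or a stated consequence. The article describes no second interim look and no hold on accrual while the first 25 patients are followed.

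**The concern.** A rule that can end a trial early for toxicity is useful to the extent that patients remain who have not yet been exposed. Here the look waits for 25 patients to complete 6 months, while the whole trial is planned to accrue in 12 months and radiation follows enrolment within about two weeks. The stated elements work against each other: by the time the rule can be applied, accrual is almost over.

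What is at stake is exposure. Patients may have up to 10 progressing sites irradiated while systemic therapy continues, and previously irradiated lesions may be retreated. The article itself says that no trial has specifically evaluated SBRT for oligoprogression in melanoma on immunotherapy. If toxicity were unacceptably high, the one rule written to react to it would do so after nearly everyone had been treated.

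**Working it through.** The plan states no figure for the number enrolled at the interim, so there is none to reproduce. The sample-size calculation does not enter; only the accrual target does.

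**Inputs**
- 52 patients in 12 months (abstract; Statistical analysis).
- Look after the first 25 have at least 6 months of follow-up (Statistical analysis).
- Radiation complete about 2 weeks (0.46 month) after enrolment (Treatment intervention; a target).
- Assumptions: uniform accrual, no hold, no time for data cleaning or review.

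**Timing on plan**
- Rate: 52 / 12 = 4.33 per month.
- Patient 25 enters at 25 / 4.33 = month 5.77.
- Earliest look: 5.77 + 6 = month 11.77.
- Enrolled by then: 4.33 × 11.77 = 51.0, so 1 is not yet enrolled.
- Radiation completed: 4.33 × (11.77 − 0.46) = 49.0, so about 3 have not completed it.

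**Sensitivity to the accrual assumption**

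| Accrual | Look (month) | Enrolled | Not yet enrolled |
|---|---|---|---|
| 52 uniform over 12 months | 11.8 | 51 | 1 |
| 52 uniform over 15 months | 13.2 | 46 | 6 |
| 52 uniform over 18 months | 14.7 | 42 | 10 |
| 52 uniform over 24 months | 17.5 | 38 | 14 |
| Front-loaded, 52 × (t/12)^0.7 | 10.2 | 46 | 6 |
| Back-loaded, exponent 1.5 or 2 | 13.4 or 14.3 | 52 | 0 |
| 44 treated (52 less 15% screen failure) over 12 months | 12.8 | 44 | 0 |

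**The present rule.** 30% of 25 is 7.5, so 8 events are needed. The binomial probability of 8 or more of 25 is 0.2%, 2.5% and 11% at true rates of 10%, 15% and 20%.

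**An earlier look.** The first CTCAE visit after radiation is at 4 weeks (± 2 weeks) in Table 2 but at about 8 weeks in the text of the same section. With 2 weeks for radiation, that visit falls 6 weeks (1.38 months) or 10 weeks (2.30 months) after enrolment.
- First 20 patients: 20 / 4.33 = 4.62. Adding 1.38 gives month 6.0, with 26 enrolled and 26 not. Adding 2.30 gives month 6.9, with 30 enrolled and 22 not.
- First 10 patients: 10 / 4.33 = 2.31. Adding 1.38 gives month 3.7, with 16 enrolled and 36 not. Adding 2.30 gives month 4.6, with 20 enrolled and 32 not.

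**Chance flags with the 30% criterion**

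| True rate | 8 or more of 25 (present rule) | 6 or more of 20 | 3 or more of 10, or 6 or more of 20 |
|---|---|---|---|
| 10% | 0.2% | 1% | 7% |
| 15% | 2.5% | 7% | 20% |
| 20% | 11% | 20% | 37% |

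The last column is the chance of at least one flag across both looks, which share the first 10 patients.

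**The case against.** The strongest reply is that this is a condensed article. It neither states nor rules out an accrual hold, and the full protocol may contain one, or a running safety review. Uniform accrual on schedule is also an assumption. At a single centre slower accrual is plausible, and over 15 to 24 months 6 to 14 patients would still be unenrolled. The 6-month window has its own purpose, since a visit at 4 or 8 weeks cannot show late toxicity or early efficacy trends. Unit monitoring and toxicity assessment at each visit are described, the treatments are presented as standard modalities, the article cites low toxicity from combining SBRT with immunotherapy, and the rule only asks that termination be considered.

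Much of this stands, and it limits the claim. A reader might infer that the rule cannot protect anyone, or that the sponsor has decided against a pause. The documents support neither. Even on plan about 1 patient is unenrolled and about 3 have not completed radiation, and on a pause the article is simply silent. A reader might also count it against the rule that 8 of 25 is reached only 49% of the time at a true rate of 30%. That is what happens whenever an observed proportion is compared with a threshold equal to the true rate, so it is no defect.

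The timing itself is not answered. Trigger, accrual period, threshold and consequence are all stated, and their combination is what fails. A safeguard should not depend on the trial missing its own accrual target, and the other provisions carry no threshold or action.

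**Conclusion.** The point holds in limited form. If accrual runs as planned, is roughly uniform and is not held, the only stated toxicity stopping rule is applied no earlier than about month 11.8, with about 51 of 52 patients enrolled and about 49 irradiated. It could spare about 1 patient from enrolment and about 3 from completing radiation. Any time for data cleaning would push the look to or past the end of accrual. Slower or front-loaded accrual leaves more patients to protect, while back-loaded accrual, or counting only 44 treated patients, leaves none to be enrolled. A hold in the full protocol would remove the problem, but none is described in the article. Since the rule as written largely misses its purpose and the trial is already enrolling, the correction should be made soon.

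**What to change.** Add at least one earlier safety look, using the acute CTCAE data already scheduled for the first visit after radiation. One example is a look when the first 20 patients have had that visit, with the sponsor's own 30% criterion (6 or more of 20) as a trigger for review. Keep the 6-month look at 25 patients for late toxicity and early efficacy. State whether accrual is held before either look. Table 2 and the follow-up text disagree on when the first visit takes place and must be reconciled, because the date of the early look depends on it.

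The cost is protocol wording and a short tabulation of data already collected, plus more chance flags. One look at 20 patients raises the flag probability at a true rate of 20% from 11% under the present rule to 20%. A further look at 10 patients (3 or more) would come earlier, with 32 to 36 still unenrolled, but raises the chance of any flag to 37%. That is acceptable only because a flag calls for review and does not stop the trial automatically. The single look at 20 is the more economical choice.
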